### Study monitoring

Serious adverse events (any hospitalization of mother or infant other than for delivery, congenital anomaly or birth defect, persistent or significant disability, death) identified by information from participants at data collection points or using pre-paid change of circumstances cards, or from HES data at the conclusion of the study, will be recorded using the NHS National Patient Safety Agency form and reported by the chief investigator (CI) to the Multicenter Research Ethics Committee, who gave a favorable opinion within 15 days of the CI becoming aware of the event.

An independent Data Monitoring Committee (DMC) has been established, whose remit is to review the trial’s progress. Interim analyses will be supplied, in strict confidence, to the DMC, as frequently as its Chair requests. The terms of reference and a DMC charter [59] including stopping guidance will be agreed at their first meeting. Meetings of the committee will be arranged periodically, as considered appropriate by the Chair. In the light of interim data on the trial’s outcomes, adverse event data, accumulating evidence from other trials and any other relevant evidence (including updated overviews of the relevant randomized controlled trials), the DMC will inform the Trial Steering Committee (TSC) if in their view there is proof beyond reasonable doubt that the data indicate that any part of the protocol under investigation is either clearly indicated or contra-indicated, either for all or for a particular subgroup of trial participants. Unless modification or cessation of the trial is recommended by the DMC, the TSC, investigators, collaborators and administrative staff (except those who supply the confidential information) will remain blind to the results of the interim analysis. Collaborators and all others associated with the study may write to the DMC via the Trial Co-ordinating Center, to draw attention to any concern they may have about the possibility of harm arising from the treatment under study.

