**Methods/Design:**

The study comprises a multi-site randomized controlled trial designed to identify the benefits of gFNP compared to standard care. Participants (not eligible for FNP) must be either aged < 20 years at their last menstrual period (LMP) with one or more previous live births, or aged 20 to 24 at LMP with low educational qualifications and no previous live births. ‘Low educational qualifications’ is defined as not having both Maths and English Language GCSE at grade C or higher or, if they have both, no more than four in total at grade C or higher. Exclusions are: under 20 years and previously received home-based FNP and, in either age group, severe psychotic mental illness or not able to communicate in English. Consenting women are randomly allocated (minimized by site and maternal age group) when between 10 and 16 weeks pregnant to either to the 44 session gFNP program or to standard care after the collection of baseline information. Researchers are blind to group assignment.

The primary outcomes at 12 months are child abuse potential based on the revised Adult-Adolescent Parenting Inventory and parent/infant interaction coded using the CARE Index based on a video-taped interaction. Secondary outcomes are maternal depression, parenting stress, health related quality of life, social support, and use of services.

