### Group Family Nurse Partnership

Group FNP was developed in 2009, jointly by the UK FNP National Unit and the US NFP National Office led by [name], as a way to use the expertise of the FNP nurses and the learning from the FNP to reach women whose children were at risk of poor outcomes but offered in a different context and to those not eligible for FNP. The newly developed program has the same theoretical basis as the home-based program but is delivered in a local children’s center (or similar community location). The aims of the gFNP program are to improve birth outcomes, develop a warm and authoritative parenting style underpinned by good attachment and knowledge of babies’ developmental needs, promote effective local support networks through contact with other parents, increase take-up of local services, and greater parental self-efficacy to make positive life choices and plan for their future through, for example, thinking about gaining educational qualifications or training for employment. While FNP continues until infants are 24 months old gFNP runs until infants are 12 months of age [26].

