The sites delivering gFNP are established FNP sites and gFNP will be delivered in addition to the one to one FNP program in those sites, to clients who would are ineligible for FNP. The program is delivered to each group by two family nurses trained according to US NFP guidelines and who are experienced in delivering home-based FNP [26], one of whom is a practising midwife. Each group comprises between 8 and 12 women, whose partners are encouraged to attend. Women using group based antenatal care such as the Centering Pregnancy Model [27], reported a preference for this approach over traditional care [28-30]. Centering Pregnancy has been associated with improved prenatal outcomes such as reductions in preterm births among high-risk women [31,32]. Following this model of delivery, gFNP provides routine midwifery care in pregnancy and infant health checks according to NICE guidelines [33] during the gFNP session with encouragement for mothers to conduct the necessary pregnancy checks themselves with guidance from the family nurses and midwives. Any out-of-hours antenatal care is managed according to local arrangements (this may involve a community midwifery team or hospital) and intrapartum care is managed by the hospital/birth center midwifery team. The group context should help mothers to develop social networks with other local mothers [34], and to benefit from peer-group learning. Also, meeting in Children’s Centers helps families to become familiar with the other services and to develop regular contact with other professionals when additional support is called for [35].

An implementation evaluation in England found that both the mode of delivery and materials were acceptable to clients and nurses [34-36]. In addition to developing relationships with the family nurses, clients have developed close relationships with group members and made regular use of other services in the Children’s Centers. The delivered content of gFNP is consistent with NFP US National Office recommendations [36] and the prediction is that gFNP is likely to be associated with the same kinds of benefits as the individually delivered program. However, in order to provide optimal information for service providers and commissioners, and to provide the most effective support for potentially vulnerable families, it is important that programs be subject to rigorous randomized trials to provide evidence about efficacy and cost-effectiveness.

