Data will be double entered to ensure quality and a percentage of completed forms reviewed for quality. All LSHTM data will be managed and stored in compliance with ICH GCP 1996 following trial specific standard operating procedures (SOP) as given in the trial master file, and in accordance with LSHTM Information Management and Security Policy and LSHTM Data Protection Policy. Anonymized data will be stored securely at the LSHTM and separately from any information identifying participants. Paper forms will be stored in numerical order in a secure and accessible place and will be maintained in storage for a period of three years after completion of the study. Electronic data will be stored as csv files and Stata data files (.dta) in LSHTM data centers which provide appropriate levels of environmental and physical security on servers that are managed in accordance with LSHTM Systems Management Policy. Confidential information will be registered with the LSHTM Archivist and Records Manager and data will be stored on a secure server which maintains an audit trail demonstrating system access. At the end of the study, routinely collected HES data for trial participants will be accessed for information on all hospital health service activity during the period between randomization and 12 month postpartum. HES data cover hospital in-patient, outpatients, and accident and emergency attendances.

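### The closed SAE definition leaves out serious maternal complications confined to the delivery stay and pregnancy losses without admission, and leaves stillbirth and neonatal care from birth unclear

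*Protocol article*

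**What the plan says.** The definition stands in brackets in the Study monitoring section: "any hospitalization of mother or infant other than for delivery, congenital anomaly or birth defect, persistent or significant disability, death". It has four criteria, and no wording such as for example or including opens the list.

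The same section gives the sources of SAE information. While the trial runs, events are "identified by information from participants at data collection points or using pre-paid change of circumstances cards". Routine hospital records are added as a last source, in the words "or from HES data at the conclusion of the study". The Data management section describes the Hospital Episode Statistics (HES) extract as giving "information on all hospital health service activity during the period between randomization and 12 month postpartum" and adds that "HES data cover hospital in-patient, outpatients, and accident and emergency attendances".

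On the programme, the Group Family Nurse Partnership section states that "gFNP provides routine midwifery care in pregnancy and infant health checks according to NICE guidelines". It leaves out-of-hours antenatal care to local arrangements and care in labour to the hospital or birth centre team. It also says "The aims of the gFNP program are to improve birth outcomes", among other things. According to the abstract, women are randomized "when between 10 and 16 weeks pregnant".

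The Aims of the study section lists infant birth status as a secondary objective. Table 1, which sets out the measures and their timing, has no row for pregnancy outcome, birth status or neonatal care. The data monitoring committee (DMC) is to weigh adverse event data together with interim outcome data when it judges whether anything under study is clearly indicated or contra-indicated.

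**The concern.** In the intervention arm the scheduled antenatal checks move into the group session, with mothers encouraged to carry out checks themselves under guidance. A foreseeable harm of such a change is a pregnancy complication that is recognised late. It may first show as a pregnancy loss, or as a serious event around the birth. These are the places where the list is thin: delivery admissions are removed, severity within a stay is not a criterion, and pregnancy loss is not named.

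At stake is whether the comparison of SAEs by arm, which the DMC uses and which would normally be reported, includes these events, and whether staff at seven sites would classify the same event in the same way.

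**Working it through.** No arithmetic decides this point. The check is to apply the four criteria, as worded, to the kinds of event that can occur between randomization and 12 months after birth.

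| Event | Criterion met | Counted as an SAE? |
|---|---|---|
| Antenatal admission for a complication | Hospitalization, not for delivery | Yes |
| Postnatal readmission of mother or infant | Hospitalization, not for delivery | Yes |
| Congenital anomaly, lasting disability, maternal or infant death | Named | Yes |
| Pregnancy loss with an admission that is not for delivery | Hospitalization | Yes |
| Life-threatening maternal complication arising in the delivery stay, with full recovery | None: the admission was for delivery, with no death or lasting disability | No |
| Miscarriage managed without admission | None: no hospitalization, and an early loss is not ordinarily recorded as a death | No |
| Stillbirth | The admission may be for delivery; the word death is unqualified and does not say whether fetal death is included | Unclear |
| Neonatal-unit care running on from birth | Can be read as infant hospitalization other than for delivery, or as part of the birth stay; prolonged stay is not a criterion | Unclear |

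Two rows therefore fall outside the list and two can be classified either way.

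The next question is whether another stated route picks these events up.

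- **Scheduled contacts.** After baseline, the first is the visit at infant age two months. The programme lasts 76 weeks on average, from 16 weeks of gestation to infant age 12 months. Taking 12 months as 52 weeks, 76 − 52 = 24 weeks fall in pregnancy. A woman randomized at 16 weeks who delivers at term thus has about 24 weeks plus two months without a scheduled contact, and a woman randomized earlier has longer. In that interval only the change of circumstances cards are available, and the next visit is timed by the age of an infant.
- **Trial measures.** Birth status is a secondary objective, but neither Table 1 nor the Secondary outcome measures section names a measure of it, of pregnancy outcome or of neonatal care.
- **HES.** The extract spans the delivery episode in both arms, so in-hospital events exist as data. But it is used for SAEs only at study end, and an event found there must still meet the definition, which removes the delivery admission. A loss without hospital contact would not appear in it.

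None of the three clearly closes the gap, and none does so for interim review.

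**The case against.** The strongest reply is that the list already covers most of what would signal poorer antenatal care: antenatal admissions for any reason, readmissions, anomalies, lasting disability, and maternal and infant deaths. That stands, and it limits the point. A reader might infer that the harms most relevant to this programme go uncounted altogether; the text does not support that.

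Three further replies also stand in part.

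- **Wording.** In the definition, mother or infant qualifies hospitalization, not death, and nothing requires an infant admission to be a new one. Stillbirth and neonatal care from birth are therefore ambiguous, not excluded.
- **Scope of the programme.** It takes over routine antenatal midwifery only, with a practising midwife as one of the two nurses. Events in labour arise under care common to both arms. This weakens the link with the programme but does not remove it, because a problem missed antenatally can surface during the delivery stay.
- **Other data.** The DMC sees interim outcome data and adverse event data generally, and the same definition applies to both arms. It would therefore be too strong to say that the published safety comparison must be falsely reassuring.

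A last reply is that a journal article condenses a fuller protocol, and that the reporting form, standard procedures or DMC charter may say more. They may. But the article does not leave the definition to those documents. It states one, and as stated it reads as complete. Excluding delivery admissions is sensible when nearly every participant has one; the difficulty is that the exclusion is not limited to uncomplicated ones.

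**Conclusion.** The point holds in a limited form. As worded, the definition does not cover a serious maternal complication confined to the delivery stay with recovery, or a pregnancy loss without admission. It leaves stillbirth and neonatal care from birth open to inconsistent classification. Some relevant harms may be missed; many are counted.

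No rate of omission can be derived from the article. A reader might assume, say, a 1% to 3% risk of pregnancy loss among 200 women, giving 200 × 0.01 = 2 to 200 × 0.03 = 6 losses, with a chance of at least one of 1 − 0.99^200 = 0.87 to 1 − 0.97^200 = 0.998. Those rates are not in the document. Moreover, the figures describe losses of any kind, including those that count through an admission or might be read as deaths. They say nothing about how many would be left out.

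The conclusion assumes that the bracketed list is applied as written and that no unseen document extends it. The remedy is cheap and improves the safety data by arm, which is reason enough to make it.

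**What to change.** Reword the definition in the Study monitoring section and on the reporting form:

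- exclude only uncomplicated admissions for delivery;
- add life-threatening events, and prolongation of a hospital stay, including the delivery stay;
- state that pregnancy loss after randomization, both miscarriage and stillbirth, is recorded whether or not there was an admission;
- state how neonatal-unit care that runs on from birth is classified.

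Tabulate pregnancy loss and neonatal-unit admission by arm, as separate lines, for the DMC and in the final report. The planned HES extract can supply or confirm the in-hospital events in both arms at study end; losses without admission need participant report.

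This changes wording and forms only, and concerns the recording of events, not clinical care. The cost is a modest rise in the number of SAE forms.

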## Discussion

The study is dependent on local community midwifery teams identifying potentially eligible participants and asking them to sign a simple form so that their contact details can be shared with the research team. Thus, it has been necessary to develop strong links with local midwifery in each site and to tailor the collection of the contact details forms to suit the way each team works. The FNP teams also have to have close links with midwifery since they are jointly responsible for delivering midwifery care to women in the intervention arm of the trial. That has meant a substantial amount of time had been required for meetings and other liaison for the research team and for each local FNP team but it is clear that without close cooperation of all local midwives the required number of eligible women in each site with EDDs (only up to six weeks apart) will not be identified in the short time frame that is necessary. We believe that the necessary groundwork has been made and hope that the next publication about this trial will concern its results, demonstrating whether there is an impact on parenting and other aspects of maternal well-being. This is the first study to examine the effectiveness of gFNP in the UK. Results should inform decision-making about its delivery to vulnerable families not eligible for FNP, potentially enabling a wider range to benefit from the FNP curriculum approach to supporting parenting.

### Trial status

Recruitment will begin in late July 2013 and continue until January 2014.

## Abbreviations

A&E: Accident and emergency unit in hospital; CI: Chief investigator; CTU: Clinical trials unit; DCE: Discrete choice experiment; DMC: Data monitoring committee; EDD: Expected delivery date; FN: Family nurse, trained to deliver FNP according to USA NFP National office guidelines; FNP: Family nurse partnership home-visiting program (UK); GCP: Good clinical practice; GCSE: General certificate of secondary education; gFNP: Group-based family nurse partnership; HES: Hospital episode statistics; HSRU: Health services research unit; ISRCTN: International standard randomized controlled trial number; LMP: Last menstrual period; LSHTM: London school of hygiene and tropical medicine; MOS: Medical outcomes study; NICE: National institute for health and clinical excellence; NFP: Nurse family partnership, the original USA developed home visiting program, renamed FNP in the UK; NHS: National health service; NIHR: NHS national institute for health research; QALY: Quality adjusted life year; RCT: Randomized controlled trial; SOP: Standard operating procedures; TSC: Trial steering committee.
